#### 6.1.2 Secondary study parameters/endpoints

- The total duration of antibiotic therapy.
- The proportion of antibiotic therapy started for suspected and, or proven EOS if symptoms started between 24-72 hours after birth.

- Quality of life: To get an impression of the impact of (suspected) early-onset sepsis on the quality of life (QoL) of both parents/guardians and their child, parents/guardians will be asked to fill in a questionnaire on day 14 after birth. Our questionnaire is based on (parts of) two questionnaires, which were used in different studies assessing the effect of early intravenous-to-oral antibiotic switch (30), and the influence of resiliency and stress on parental/guardian perspective of the future QoL of their newborns (31). The first part collects information on medical factors after hospitalization (side effects, number of medical visits, readmission, and medication use) and basic needs of the newborn (sleep quality of the patient, (breast)feeding success rate). The second part addresses the subjective parental/guardian evaluation of the impact of newborns' admission, and parental/guardian projection of future QoL of their newborn. The last part of the questionnaire collects demographic data. We hypothesize that the maternity period is experienced more positive if mother and child go home quickly, because of less hinder to take care of their child (for example, earlier initiation of breastfeeding), and less stress (for example, emotionally or financially). The questionnaire is designed in close collaboration with Care4Neo. Care4Neo (formerly Association of Parents of Incubator Children) represents the interests of parents/guardians whose child is admitted to a hospital immediately after birth.

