## 1. INTRODUCTION AND RATIONALE

Newborns are at risk for early-onset sepsis (EOS) (1,2). A (suspected) EOS is defined as a (suspected) infection that develops within 72 hours after birth. The incidence of confirmed EOS is 0.5-2.0 per 1000 live births. For the Netherlands, this translates to approximately 85-340 EOS cases yearly.

Suspicion of EOS is often based by doctors on risk factors and nonspecific clinical symptoms, such as maternal fever during labor or rapid breathing in the newborn. The classic infection parameters in the blood of newborns are of little to no value to rule out an infection at the time of presentation (3). The combination of the difficulty to recognize EOS in time and the risk of serious consequences of EOS not treated timely has resulted in a low threshold for the start of empirical antibiotic treatment. This has led to significant overtreatment; it is estimated that in the Netherlands about 5% of all newborns receive antibiotic therapy for suspected EOS, equivalent to 8,500 newborns per year (4–6), compared to the estimated 85-340 of confirmed EOS cases. Adverse consequences of antibiotic overtreatment are increasingly recognized (4). In the short term, it leads to separation of parents and newborn, invasive painful procedures (with possible long-term consequences for brain development), and unnecessary hospitalization with associated costs. In the longer term, there are significant disadvantages for the microbiome and immune system, found to be associated with obesity (7), eczema, asthma (8,9), and diabetes later in life (10). In addition, at the population level, overuse of antibiotics leads to resistant infections that are difficult to treat.

The current standard of care is the NVK guideline "Prevention and treatment of early-onset neonatal infections" (11). The aim of this guideline is uniform, evidence-based, diagnosis and treatment of early-onset neonatal infections, including careful use of antibiotics. The NVK guideline is an adaptation of the 2012 version of the National Institute for Health and Care Excellence (NICE) guideline "Antibiotics for early-onset neonatal infection: antibiotics for the prevention and treatment of early-onset neonatal infection" (12).

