For the Dutch situation, equipoise between the current guideline and the EOS calculator can be established given balance of risk for both over- and undertreatment of EOS for both strategies: the current guideline is likely to result in more overtreatment with adverse consequences, but potentially carries a smaller risk for treatment delay (although it is unclear to what clinical significance). A large body of evidence now supports the safety of the EOS calculator approach, but validation outside of the North-American setting is limited, especially for safety outcomes. Equipoise between both strategies is confirmed by the recently updated version of the NICE guideline (the NVK guideline was based on the 2012 version), which includes use of the ‘EOS calculator’, as a valid alternative approach to allocate antibiotics to newborns.(19) Equipoise can also be inferred from recommendations of the American Academy of Pediatrics, which considers both a risk-factor based approach and the EOS calculator as valid strategies. We compared the EOS calculator to the NVK guideline in a post-hoc analysis of our multicenter study (20), and found that the EOS calculator recommended significantly fewer antibiotics than the NVK guideline. This result is in line with the results of previous international research showing that the EOS calculator is proven to be effective and safe for reducing antibiotic overtreatment (17,21).

A prospective cluster-randomized Dutch validation study of the EOS calculator is needed before complete adoption of the EOS calculator, because of the following reasons:

1) Multicenter validation of actual EOS calculator use has not been performed in the Netherlands.

2) To date, no randomized prospective study of EOS calculator use with safety as an outcome measure has been performed. Specifically, there are no studies that take into account the potential effects of a treatment delay due to EOS calculator use. This especially holds true for cases that are clinically suspect for EOS, but not culture-confirmed. The study here proposed by us is, to the best of our knowledge, the first.

This protocol describes a cluster-randomized trial, which is the logical next step to our previous research (18,22–28). The study aims to investigate whether the use of the EOS calculator safely reduces antibiotic exposure in newborns with suspected EOS compared to the current Dutch guideline.

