### 4.2 Inclusion criteria

In order to be eligible to participate in this study, a subject must meet all of the following criteria:

- postmenstrual age of 34 weeks or more;
- age between 0-24 hours;
- at least one EOS risk factor or clinical sign of infection (suspected of EOS) present within the first 24 hours of life (Table 1);
- parental/guardian consent.

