#### **5.4 Summary of known and potential risks and benefits**

**Benefit:** Meta-analysis shows up to an average of 44% less antibiotic use, without indications of negative consequences (17).

**Risk:** We like to address that the use of the EOS calculator is not able to capture all newborns with a proven EOS, comparable to any other guideline. It is important to realize that missed cases does not mean that the missed cases have died or have a worse outcome. It means that antibiotics were not started immediately after birth. The EOS calculator-based strategy is therefore not automatically inadequate or less safe, but it indicates that the calculator relies to a greater extent on clinical observation for 24 hours that is advised by the calculator. Achten et al. reviewed all cases of EOS in a meta-analysis. Among before-after implementation studies, they found 5 of 18 (28%) “missed” cases in cohorts with EOS calculator-based management, compared to 8 of 28 “missed” cases (29%) in cohorts with conventional management strategies. All newborns with “missed” EOS were eventually started on antibiotics. To have no missed cases, we must treat all babies after delivery, which is undesirable because we know that antibiotics early in life do harm.

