## 6. METHODS

### 6.1 Study parameters/endpoints

#### 6.1.1 Main study parameter/endpoint

**Co-primary superiority outcome:** The proportion of patients that started antibiotic therapy for suspected and, or proven EOS in the first 24 hours after birth.

**Co-primary non-inferiority outcome:** A composite non-inferiority outcome regarding the presence of one or more of the following four predefined safety criteria, namely 1) the need for any respiratory support, and/or 2) the need for an intravascular fluid bolus for hemodynamic instability due to sepsis, and/or 3) referral to a Neonatal Intensive Care Unit for sepsis treatment, and/or 4) proven EOS.

- Respiratory support is defined as any form of respiratory support (invasive ventilation, continuous positive airway pressure (CPAP), high flow nasal cannula (HFNC), low flow oxygen) during the first week of life.
- Intravascular fluid bolus is defined as the intravenous administration of a fluid bolus of 10ml/kg within 15-30 minutes. It is the first step in the treatment of hemodynamically unstable newborns due to sepsis.
- Proven EOS is defined as a blood or cerebrospinal fluid (CSF) culture obtained within 72 hours after birth growing a pathogenic bacterial species.

The mentioned co-primary outcome criteria overlap with non EOS causes. For example, prematurity is also associated with the need for respiratory support or asphyxia with the need for intravascular fluid administration. It is for this that a randomization trial was chosen. We do not expect that a reduction in antibiotic exposure by using the EOS calculator will lead to significantly more of these outcomes. Because the trial is not blinded, there is a change that (unconscious) bias may occur. We expect that this will be limited by the cluster-randomized design on the one hand, and by the relatively objective criteria, on the other hand.

Furthermore, we decided for a composite non-inferiority outcome, based on four predefined criteria, since the incidence of each individual criterion is very low.

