### 7.2.2 Serious adverse events (SAEs)

A serious adverse event is any untoward medical occurrence or effect that

- results in death;
- is life threatening (at the time of the event);
  - o except, if it concerns neonatal (advanced) life support directly after birth;
  - o except if it concerns surfactant therapy;
  - o except referral to a NICU:
    - (need for mechanical ventilation because of) surfactant therapy;
    - insertion of central venous lines;
    - respiratory support for prematurity.
- requires hospitalization or prolongation of existing inpatients' hospitalization;
  - o unless a newborn will start with antibiotic therapy for (suspected) EOS during the observation period or after discharge, but within 72 hours after birth. See also 5.4.;
  - o unless it is due to prematurity.
- results in persistent or significant disability or incapacity; or
- any other important medical event that did not result in any of the outcomes listed above due to medical or surgical intervention but could have been based upon appropriate judgement by the investigator.

Referral to a NICU will be included in the electronic Case Report Form (eCRF), since this is one of the non-inferiority criteria.

Each study site will report all SAEs to the coordinating investigators within 24 hours after becoming aware of the event. The coordinating investigators will report all SAEs to the sponsor without undue delay after obtaining knowledge of the events. The sponsor will report the SAEs through the web portal *ToetsingOnline* to the accredited METC that approved the protocol, within 7 days of first knowledge for SAEs that result in death or are life threatening followed by a period of a maximum of 8 days to complete the initial preliminary report. All other SAEs will be reported within 15 days after the sponsor has first knowledge of the serious adverse events.

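### On the plain reading, an antibiotic start after 24 hours for signs present earlier, or without symptoms, falls in neither antibiotic-start endpoint

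*Protocol*

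**What the plan says.** Protocol 6.1.1 gives the co-primary superiority outcome as "The proportion of patients that started antibiotic therapy for suspected and, or proven EOS in the first 24 hours after birth". Protocol 6.1.2 gives the endpoint for later treatment as "The proportion of antibiotic therapy started for suspected and, or proven EOS if symptoms started between 24-72 hours after birth". The Summary defines both outcomes in the same way, and Section 2 repeats the symptom-onset condition for the secondary.

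The only other antibiotic endpoint is "The total duration of antibiotic therapy" (6.1.2).

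Four other statements bear on the point:

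- Section 1 sets the disease window: "A (suspected) EOS is defined as a (suspected) infection that develops within 72 hours after birth".
- Section 4.2 admits newborns with "at least one EOS risk factor or clinical sign of infection (suspected of EOS) present within the first 24 hours of life".
- Section 1, among the reasons for the trial, says "there are no studies that take into account the potential effects of a treatment delay due to EOS calculator use".
- Section 5.4 says that "the calculator relies to a greater extent on clinical observation for 24 hours".

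**The concern.** The co-primary appears to run on the time at which antibiotics start, and the secondary on the time at which symptoms start. Two endpoints on different clocks do not divide the later treatment between them, so some starts within the EOS window have no place in either.

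The trial asks whether the calculator safely lowers antibiotic exposure. A start moved past 24 hours is deferred, not avoided, but the co-primary would record it as no start and the secondary would not pick it up. The protocol gives treatment delay as one reason for doing the trial, so deferred starts should be visible by arm.

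**Working it through.** **1. Which endpoint holds which newborn.** The plain reading takes the 24-hour phrase in the co-primary to time the start of treatment. The other reading takes it to time the suspected or proven EOS.

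| Newborn | Plain reading | Other reading |
|---|---|---|
| Signs at 10 h, start at 14 h | Co-primary | Co-primary |
| Signs at 20 h, start at 26 h | Neither | Co-primary |
| Maternal risk factor only, first signs at 26 h, start at 27 h | Secondary | Secondary |
| No symptoms, start at 26 h | Neither | Not settled |

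The gap on the plain reading is rows two and four. Row four can occur. The red flags in Table 1 include infection in another neonate of a multiple pregnancy, and maternal parenteral antibiotics for suspected or confirmed invasive infection up to 24 hours after birth. Neither is a symptom of the newborn.

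**2. What the gap does to the estimate.** For each arm, as proportions of all included newborns, let A be starts at 0-24 h, B starts after 24 h with symptom onset at 24-72 h, and G starts after 24 h and within 72 h that are in neither endpoint. Then:

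- all starts by 72 h: T = A + B + G
- reduction seen in the two endpoints together: (A+B) control − (A+B) calculator = [T control − T calculator] + [G calculator − G control]

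Only the between-arm difference in G matters. With B equal in the two arms, each point of that difference adds one point to the apparent reduction in the co-primary. If G is equal in both arms, there is no bias.

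**3. The plan's own figures.** Section 4.4 gives 40% against 25%, 80% power, ICC 0.0025, alpha 0.05 and 10 hospitals. The two-proportion formula with two-sided alpha gives 152 per arm. The design effect at 33 per hospital is 1 + 32 × 0.0025 = 1.08, and 2 × 152 × 1.08 = 328, against 330 stated. The figure reproduces and is not in dispute.

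**4. Illustration on an assumption.** The protocol gives no rate of deferred starts. Suppose 40% start by 72 h in both arms, so that there is no true reduction, and an excess of d points in the calculator arm falls in the gap. At the non-inferiority total of 1640, the design effect is 1 + 163 × 0.0025 = 1.4075, so the effective number per arm is 820 / 1.4075 = 583. A normal approximation gives the chance of p<0.05 in favour of the calculator on the co-primary:

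| d (points) | Share of starts, d/40 | Chance |
|---|---|---|
| 1 | 2.5% | 5% |
| 2 | 5% | 10% |
| 3 | 7.5% | 18% |
| 5 | 12.5% | 42% |
| 10 | 25% | 95% |

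Section 8.1 also asks for an absolute reduction of at least 15 points. Delay alone would meet that only if 15/40 = 37.5% of starts slipped. Delay could still lift a smaller real reduction: a true reduction of 15 − d points with d points displaced shows as 15.

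**5. Do other measures show the deferred starts?** Total duration carries no information on when treatment began. The safety composite in 6.1.1 captures proven EOS by a positive culture within 72 h, and some clinical consequences, but not a late start for culture-negative suspected EOS. Readmission for EOS is collected (6.3) but is not an endpoint.

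**The case against.** The strongest reply is that the gap depends on how one sentence is read. Objective 1 in Section 2 and the design text in Section 3 both speak of EOS suspected within the first 24 hours. If the co-primary follows them, the two endpoints split by onset at 24 hours, and the calculator's validation only for that period gives a reason for the split. This stands as a possible reading. It would close the gap for early symptoms, but the protocol does not settle it.

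A reader might go further than the text allows in five ways:

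- **That deferred starts will cluster in the calculator arm.** Section 5.4 makes this possible, but both arms observe newborns with three-hourly vital signs, and calculator-arm newborns are re-examined within 24 hours. The only figures given are missed proven cases: 5 of 18 (28%) with the calculator and 8 of 28 (29%) with conventional management. They are few and culture-proven only, and they show no excess.
- **That the reduction is overstated by a known fraction.** Any such figure restates an assumed rate.
- **That every newborn observed for a risk factor alone is lost.** If signs first appear after 24 hours, the secondary counts the start.
- **That delayed starts escape SAE reporting.** The exception in 7.2.2, "unless a newborn will start with antibiotic therapy for (suspected) EOS during the observation period or after discharge, but within 72 hours after birth", qualifies only the hospitalization criterion and applies in both arms. The other SAE criteria still apply, and adverse events are recorded to day 14 (7.2).
- **That the effects of delay go unmeasured.** The co-primary safety composite addresses effects. What is not counted is the deferred start itself.

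**Conclusion.** The concern holds as a flaw of endpoint definition. On the plain reading, starts after 24 hours for earlier signs, and starts after 24 hours without symptoms, belong to neither antibiotic-start endpoint. On either reading, the protocol names no endpoint covering all starts within the 72 hours that define EOS.

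The effect on the estimate is one point of apparent reduction per point of between-arm difference in such starts. The documents give neither the rate nor the difference, so the size is unknown and may be small. The chances tabulated above rest on an assumed excess in the calculator arm with no true reduction by 72 hours, and on a normal approximation with only 10 hospitals. They show sensitivity and are not a forecast. Delay alone is unlikely to produce the 15-point threshold; the realistic risk is an inflated estimate. No sample-size figure is affected.

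**What to change.** 1. State in 6.1.1, the Summary and Section 2 that the co-primary is defined by time of antibiotic start, 0-24 hours after birth.
2. Redefine the secondary as antibiotic start for suspected or proven EOS at >24-72 hours, irrespective of symptom onset.
3. Use all included newborns as the denominator for both, so that the two proportions add up.
4. Report any start within 0-72 hours by arm as a supportive analysis. It should not be a condition for success, because that would make it a third co-primary.

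The split by symptom onset can stay as a breakdown of the late starts.

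The cost is rewording two endpoints and one extra analysis. Section 6.3 already provides for date and time of birth and for antibiotic data. It does not list the time of the first dose by name, but a co-primary defined by start time cannot be computed without it. The sample size does not change. The wording should be settled before outcomes are compared by arm.

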## **6.2 Randomization, blinding and treatment allocation**

Randomization will take place at cluster level for either the EOS calculator or control (antibiotics administration according to NVK directive usual care). Centers will be randomized as clusters using a computer-generated algorithm. After randomization, the hospital will also switch to the protocol assigned after randomization (NVK guideline or EOS calculator use). This assigned protocol is standard care for newborns with suspected EOS during the study period in that hospital. This is independent of participating in this study (see chapter 3). Thus, hospitals nor physicians are blinded for the assigned study protocol. However, physicians may always opt for clinical management not according to the assigned study protocol.

## **6.3 Study procedures**

For all included newborns, maternal and neonatal data on risk factors will be collected. The newborn's date and time of birth will be collected because the most important collected parameters are time dependent and need these date and time of birth as a reference. Physical examinations of the newborn will be performed at least twice (at birth and before discharge), and more often if necessary (depending on clinical findings). Finally, for

participating newborns, a single (online) questionnaire will be sent (via Castor EDC) to the parents/guardians to fulfill on day 14 after birth. The questionnaire includes a minimum of 22 questions, which may expand up to 32 questions (since some questions are dependent of other questions). It will take about 10-15 minutes to complete.

For newborns without antibiotic therapy, clinical observation for at least 12-24 hours will be performed: vital parameters (heart rate, respiratory rate, and temperature) will be measured 1, 3, 6, 9, 12, 15, 18, 21 and 24 hours after birth. This is part of standard medical treatment. Data on physical examinations will be collected. Data on readmission for suspected or proven EOS will be collected.

For newborns with intravenous antibiotic therapy, two blood samples will be taken: during insertion of the intravenous cannula before starting antibiotics (blood culture; blood cell count, CRP), and approximately 24-36 hours after the start of antibiotics by capillary or vena puncture (CRP). This is part of standard medical treatment. Duration of hospital stay will be at least 24-36 hours, could be extended depending on the clinical condition and blood culture results and non-EOS factors. During admission the need for any kind of respiratory support and the need for intravascular fluid administration will be recorded daily. Referral to a neonatal intensive care unit (NICU) will be recorded and relevant clinical data during NICU admission will be obtained by the main investigator or the research nurse/assistant of the participating hospital. Data on sort and duration of antibiotic therapy and blood culture results will be collected.

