**Burden:** -Newborns who receive antibiotic therapy: An intravenous cannula will be inserted for antibiotic treatment and blood sampling. A second blood sample by venipuncture will be collected after 24 hours. This is part of standard medical treatment. One questionnaire will be sent to the parents/guardians to fulfill on day 14, which is extra for this study. The questionnaire includes a minimum of 22 questions, which may expand up to 32 questions (since some questions are dependent of other questions). It will take about 10-15 minutes to complete. - Newborns who do not receive antibiotic therapy: No blood samples taken. Clinical observation for at least 12-24 hours. This is part of standard medical treatment. **Risks:** -The risks

associated with participation are very low because newborns will be closely observed when no antibiotics will be prescribed. **Benefits:** -More specific risk analysis. Not all subjects will benefit personally from study participation. When no antibiotics will be prescribed: no separation of mother and child, no painful procedures, and a shorter hospital stay (including fewer costs), and no unnecessary exposure to antibiotics. **Group relatedness:** This study can only be performed with this specific group of patients, as it will provide age-specific and risk factor-specific data that cannot be obtained otherwise.

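### Section 6.3 prescribes recording of respiratory support and fluids only for antibiotic-treated newborns, so any under-recording in untreated newborns would bias the safety comparison towards non-inferiority

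*Protocol*

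**What the plan says.** Protocol section 6.3 sorts data collection into three groups.

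- **All included newborns:** risk factors, date and time of birth, physical examinations and the day-14 questionnaire. No component of the safety composite is listed.
- **Untreated newborns:** "For newborns without antibiotic therapy, clinical observation for at least 12-24 hours will be performed". A vital-sign schedule and examination data follow, and then: "Data on readmission for suspected or proven EOS will be collected".
- **Treated newborns:** the paragraph opens "For newborns with intravenous antibiotic therapy, two blood samples will be taken" and later says: "During admission the need for any kind of respiratory support and the need for intravascular fluid administration will be recorded daily". NICU referral and blood culture results are also listed here.

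Section 6.1.1 defines the co-primary safety composite without regard to treatment. Its list of qualifying respiratory support ends with "low flow oxygen) during the first week of life". On culture it says: "Proven EOS is defined as a blood or cerebrospinal fluid (CSF) culture obtained within 72 hours after birth growing a pathogenic bacterial species". The Summary adds: "Newborns who do not receive antibiotic therapy: No blood samples taken".

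Three other places bear on the point. Section 7.2.2 puts NICU referral in the eCRF because it is a non-inferiority criterion, with no restriction to treated newborns. Section 10.1 says that the eCRF holds what is needed to evaluate the endpoints. Section 9.2 obtains consent to use the medical records of mother and child.

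**The concern.** The procedures do not match the endpoint. A site that follows section 6.3 literally would record respiratory support and fluids daily in treated newborns and would have no such instruction for the rest. After discharge, the only clinical item listed for an untreated newborn is readmission labelled as EOS. A first-week readmission with oxygen or CPAP under another label meets the section 6.1.1 definition but is not on that list.

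Antibiotic exposure is what the intervention is meant to change, so a data-collection rule that depends on exposure also depends on arm. Events missed in untreated newborns would lower the recorded rate more in the calculator arm. In a non-inferiority comparison that works in favour of the claim. Section 6.1.1 relies partly on relatively objective criteria to limit bias in an unblinded trial, but objective criteria do not help if they are looked for unequally.

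**Working it through.** **1. The plan's own sample size.** Inputs from section 4.4: 10% events in both arms, margin 5 points, alpha 0.025 (taken as one-sided), power 80%, ICC 0.0025, 164 per cluster, 10 hospitals.

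- Per arm without clustering: (1.960 + 0.842)² × (2 × 0.10 × 0.90) / 0.05² = 566.
- Design effect: 1 + 163 × 0.0025 = 1.4075.
- Total: 2 × 566 × 1.4075 = 1593, within 3% of the stated 1640.
- Drop-out: 164 / 0.9 = 182.2, so 183 × 10 = 1830, as stated.

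The plan's figures reproduce. The same design effect and 5 × 164 = 820 per arm are used below.

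**2. Untreated share by arm.** Section 4.4 expects 40% and 25% on antibiotics, so 60% of control and 75% of the calculator arm are untreated.

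**3. Effect of missed events.** Let m be the fraction of events in untreated newborns that goes unrecorded, and u the share of an arm's events that falls in untreated newborns.

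- Recorded rate = true rate × (1 − m × u).
- SE of log RR = √{1.4075 × [(1 − pC)/(820 pC) + (1 − pT)/(820 pT)]}.
- Chance of declaring non-inferiority = Φ{[ln 1.5 − ln(recorded RR)]/SE − 1.960}, using the section 8.1 criterion (upper 95% bound of the RR not above 1.5).

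The true rates are set at the margin, 10% and 15%. The documents do not give m or u. Assume that events fall evenly, so u = 0.60 (control) and 0.75 (calculator).

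| m | Control recorded | Calculator recorded | RR | SE | Chance of declaring non-inferiority |
|---|---|---|---|---|---|
| 0 | 10.0% | 15.0% | 1.50 | 0.159 | 2.5% |
| 10% | 9.4% | 13.9% | 1.48 | 0.165 | 3.1% |
| 25% | 8.5% | 12.2% | 1.43 | 0.176 | 4.4% |
| 50% | 7.0% | 9.4% | 1.34 | 0.198 | 8.2% |

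**4. Uneven placement of events.** Suppose that only 10% or 25% of control-arm events are in untreated newborns, and that the 15 points who lose treatment carry the risk of treated newborns. The calculator share is then u + (1 − u) × 15/40.

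- 0.10 + 0.90 × 0.375 = 0.4375. With m = 50%: 9.5% against 11.7%, RR 1.23, chance about 21%.
- 0.25 + 0.75 × 0.375 = 0.531. With m = 50%: 8.75% against 11.0%, RR 1.26, chance about 16%.

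**5. Culture alone.** The Summary gives 0.5–2.0 proven EOS per 1000 births, and section 4.1 gives 20% with suspected EOS. Assume that all cases arise in that 20%.

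- Rate among participants: 0.0005/0.2 to 0.002/0.2, that is 0.25% to 1.0%, or 2.1 to 8.2 cases per 820.
- If the 15-point shift goes uncultured at average risk, 0.15 × 2.1 to 0.15 × 8.2 = 0.3 to 1.2 cases are hidden.
- A calculator rate of 15% becomes 14.96% to 14.85%, and the chance of declaring non-inferiority moves from 2.5% to about 2.6–2.9%.

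**The case against.** A reader might infer that fewer safety events are in fact captured in the calculator arm. The protocol does not say so. The inference rests on where the sentences stand; nothing states that these events go unrecorded in untreated newborns, and the sentences themselves carry no treated-only qualifier. Section 7.2.2 puts NICU referral in the eCRF for everyone. Sections 9.2 and 10.1 allow endpoint data to be taken from the records of all participants. Section 7.2 collects adverse events to day 14, and the questionnaire asks about readmission. Section 3 promises equal monitoring, with a minimum observation in the calculator arm at least as long as in control.

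The route to lost harm is also narrower than it first looks. An observed newborn who deteriorates and starts antibiotics is cultured then and comes under the treated paragraph. The fluid-bolus and NICU components are tied to sepsis, so they would be unusual in a newborn who is never treated.

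Most of this stands. It largely settles NICU referral and makes the culture gap small. It does not settle respiratory support. Access to records and a general statement about the eCRF do not say what is extracted, or until when. Equal monitoring in section 3 is spelled out as heart rate, respiratory rate, temperature and two examinations. The questionnaire is parent-reported, and the serious-event definition exempts some hospitalizations.

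**Conclusion.** The concern holds as a risk of differential ascertainment, not as a demonstrated bias. Section 6.3 prescribes less recording for untreated newborns than the section 6.1.1 composite needs, and the imbalance in untreated newborns (60% against 75%) fixes the direction: towards non-inferiority. The main exposure is respiratory support in newborns who are never treated, including after discharge.

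The size depends on an unknown miss rate. With no missed events there is no bias. With events falling evenly and misses of 10%, 25% and 50%, the chance of declaring non-inferiority at a true RR of 1.5 is about 3.1%, 4.4% and 8.2% instead of 2.5%. Uneven placement with a 50% miss gives 16–21%. These are normal approximations under stated assumptions. The culture component alone gives only 2.6–2.9%.

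A more dramatic illustration is tempting. Suppose that always-treated newborns carry 6.25 of the 10 event points, those treated only under the guideline carry 0.75, and the remaining 60% carry 3.0. If nothing were recorded in untreated newborns, control would show 6.25 + 0.75 = 7.0% and the calculator 6.25%, an RR of 0.89 where the truth is 1.0. That requires every event in untreated newborns to be missed, which no part of the protocol supports.

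**What to change.** In section 6.3, move the recording of respiratory support, fluid bolus and NICU referral to the paragraph on all included newborns. State that these items are extracted identically in both arms from the health record through day 7, irrespective of antibiotic exposure and including readmission for any reason.

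As a minor addition, report the number of newborns cultured by arm and a sensitivity analysis of the composite without proven EOS. Both can sit in the statistical analysis plan.

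The cost is a change of wording and a few more eCRF fields for untreated newborns, with no extra tests or visits.
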